### Safety outcomes

At baseline and at each study visit, safety checks will be performed on the patients by evaluating the vital signs, complete blood count and general urine analysis, fecal occult blood test, hepatic function and renal function, and electrocardiogram results. Any adverse event that occurs during the study are observed and recorded in detail.

### Adverse event reporting

An adverse event (AE) refers to any syndrome or disease that appears or worsens during the study. The investigators record any AE in the AE form timely, including occurrence time, severity, duration, the measures taken, and the outcome. Relevant information should be submitted to the sponsors, ethics committees, and drug supervision and administration department in accordance with the regulation. The incidences of serious AEs in patients are promptly reported to the principal investigator and the adverse drug reactions to the monitoring center of the local authority within 24 h.

### Statistical analysis

No interim analysis or subgroup analyses are planned for this trial. Full analysis set (FAS), per-protocol set (PPS), and safety analysis set (SS) will be conducted. FAS refers to the ideal set of eliminating of all subjects in a minimum and reasonable manner, according to the principle of intention-to-treat (ITT). PPS is a subset of ITT’s dataset, which has completed relevant observation according to the program requirements. The compliance of these subjects ranges from 80 to 120%, in which the subjects do not seriously violate the research program, complete all visits and CRF filling, and do not miss the main evaluation indexes and most other evaluation indexes. SS refers to all subjects who receive at least one treatment after randomization. All safety information records of subjects will be evaluated, including adverse events, severe adverse events, and clinically significant changes in safety indicators. The statistical analysis is performed in a blinded manner using the SPSS 20.0 software. For the continuous variables, the chi-squared test or Fisher’s exact test is used to compare the clinical improvement, oxygen saturation, and Acute Physiology and Chronic Health Evaluation (APACHE-II) score. Relative risk, risk difference, and number of treatments are reported with a 95% confidence interval. For the two categorical variables, we make comparison between groups and calculate the 95% CI using chi-squared tests. For the repeated measures data, category variance outcomes are analyzed using generalized estimating equations, and conclusions are drawn according to the estimating of parameter and standard error.

Our approach is to use the final observation status when no mortality is observed for 14 days, to ensure that we do not lose data about the primary outcome and the key secondary outcome. A *P* value < 0.05 is considered as statistically significant.

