### Sample size

A previous study [26] on COVID-19 by traditional Chinese medicine showed that the clinical cure rate in the conventional treatment group was 61.11%, while it was 91.18% in the group receiving traditional Chinese medicine plus routine treatment. According to the literature, presuming that the rate of the clinical effective rate in the treatment group is improved from 61.11 to 91.18%, the sample size is calculated according to the parameters *α* = 0.05 (two-sided test) and *β* = 0.1. Comparing the rates of the two groups with respect to the sample size estimation formula, we calculated that 41 patients should be recruited in each group. Studies with a similar patient population have the drop-out rate of 10% [27], and we will enroll a total sample size of 160 participants. We used the calculation tool on https://www.cnstat.org/samplesize/.

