### Interventions

The Shenhuang granule comprises 50 g of *Panax ginseng C. A. Mey*, 40 g of *Rheum palmatum L.* stem, 30 g of *Sargentodoxa cuneata* stem, 30 g of *Taraxacum mongolicum*, 50 g of *Aconiti Lateralis Radix Praeparata*, and 6 g of Whitmania pigra Whitman, which are packaged into two sachets. Patients in both groups can retain standard care according to the “Guidelines for the Diagnosis and Treatment of Novel Coronavirus (COVID-19) Infection (Trial Version 7)” by the National Health Commission [8]. The treatment group will be given standard Western medicine therapy and Shenhuang granule (oral, two sachets per day) for 14 days, while the control group only receives standard Western medicine therapy for 14 days. The routine care should include early fluid resuscitation, antimicrobial anticoagulants, nutritional support, and other treatments. The Shenhuang granule is provided and manufactured by the Beijing Tcmages Pharmaceutical Co., LTD (Number: Jing 20180032). Both groups then undergo a 14-day treatment. The use of all medication information is documented in the case report form (CRF).

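### The per-protocol rule drops patients who die before day 14 (and perhaps early discharges), and its compliance range is undefined for controls, so that set carries a bias risk of unknown size and direction

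*Protocol article*

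**What the plan says.** The Statistical analysis section names three sets: FAS, PPS and a safety set. The PPS is a subset of the intention-to-treat data, restricted as follows: "The compliance of these subjects ranges from 80 to 120%, in which the subjects do not seriously violate the research program, complete all visits". It also requires completed case report forms and no missing main evaluation index. The section does not say what compliance is a percentage of, and makes no exception for death or discharge.

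Four other places bear on this rule:

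- The abstract (Methods/design) sets assessments at baseline and days 3, 5, 7 and 14.
- Outcomes and measurements makes death level 6 and discharge alive level 1 of the primary scale. Discharge counts as improvement.
- Interventions gives the granule arm two sachets a day for 14 days, "while the control group only receives standard Western medicine therapy for 14 days".
- Monitoring of compliance asks that contact be kept after transfer or discharge, in wording tied to the end of the drug treatment period.

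The FAS is introduced thus: "FAS refers to the ideal set of eliminating of all subjects in a minimum and reasonable manner". The same sentence goes on to invoke the intention-to-treat principle.

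**The concern.** A per-protocol set should exclude patients for departing from the protocol, not for reaching an outcome. A patient who dies on day 6 has departed from nothing, but cannot attend on days 7 and 14. Under the literal rule the PPS loses primary-outcome failures and can say nothing about deaths before the last visit. If discharged patients do not return for assessments, it loses successes as well.

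The compliance range adds a second selection that may differ by arm. Sachets can be counted in the granule arm. In the control arm the text gives nothing to count. A granule patient who stops because of an adverse event or deterioration may be excluded, while a comparable control stays in. What is at stake is whether the PPS result can be read as support for the FAS result.

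**Working it through.** **The plan's own figure.** The PPS rule has no figure attached. The sample size is the only calculation in the plan, and its control rate is used below, so it is reproduced first. Inputs from the Sample size section: "presuming that the rate of the clinical effective rate in the treatment group is improved from 61.11 to 91.18" per cent; "the sample size is calculated according to the parameters *α* = 0.05 (two-sided test) and *β* = 0.1"; result "we calculated that 41 patients should be recruited in each group".

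Pooled formula, no continuity correction: n = [z₀.₉₇₅·√(2p̄q̄) + z₀.₉₀·√(p₁q₁ + p₂q₂)]² / (p₂ − p₁)²

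- p̄ = (0.6111 + 0.9118)/2 = 0.76145, so √(2p̄q̄) = √0.3633 = 0.6027
- √(p₁q₁ + p₂q₂) = √(0.2377 + 0.0804) = 0.5640
- n = (1.960 × 0.6027 + 1.282 × 0.5640)² / 0.3007² = 40.1, rounded up to 41. The figure reproduces.

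**Who the visit condition removes.** The last visit is day 14. Death before then makes it impossible to attend, so exclusion is certain under the literal text. Discharge before then does not make attendance impossible. Exclusion depends on whether the remaining assessments are done, which the article does not settle.

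**Who the compliance condition removes.** Two sachets × 14 days = 28 sachets. If the denominator is the full course (an assumption), 80% is 22.4, so at least 23 sachets are needed, reached on day 12. A granule patient who dies or stops before then fails. If the denominator is doses due (the other possible reading), a patient who dies on day 5 having taken every dose scores 100% and passes this condition. Neither reading gives a value for a control.

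**Size.** The documents give no death or early-discharge shares, so the shares below are assumptions. Also assumed: a true improvement rate of 61.11% in both arms, every death a non-improver and every early discharge an improver. With m the share removed as deaths and e the share removed as early discharges,

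PPS rate = (0.6111 − e) / (1 − m − e)

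| m | e | PPS rate | Change from 61.11% (points) |
|---|---|---|---|
| 5% | 0 | 64.3% | +3.2 |
| 10% | 0 | 67.9% | +6.8 |
| 20% | 0 | 76.4% | +15.3 |
| 10% | 10% | 63.9% | +2.8 |
| 10% | 20% | 58.7% | −2.4 |
| 10% | 30% | 51.9% | −9.3 |

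- Equal removal in both arms with no true effect: the difference stays 0.
- Deaths of 10% in one arm and 5% in the other, both dropped: 67.9 − 64.3 = 3.6 points in favour of the arm with more deaths. For 20% and 10%: 76.4 − 67.9 = 8.5 points.
- Non-improvers removed from the granule arm alone, as a one-arm compliance screen could do: false differences of +3.2, +6.8 and +15.3 points for 5%, 10% and 20% removed.
- Early discharges removed as well: the rate falls, and the sign can reverse.

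**The case against.** The strongest reply is that this concerns a supporting set. The FAS follows intention to treat, Patient withdrawal keeps withdrawn patients' data for the day-14 efficacy analysis, and the last observed status is carried to day 14 when no death is seen. Nothing says the PPS carries the conclusion, and naming the primary set is commonly left to an analysis plan. This stands: neither the FAS wording nor the absence of a named primary set is a finding here. It does not repair the PPS rule, which the article itself states.

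Three stronger readings are tempting, and the documents do not support them.

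- **Early discharges are removed.** No text says that visits or treatment stop at discharge, and contact afterwards is foreseen. On the other side, that contact is tied to the end of treatment, and each visit needs laboratory tests and an electrocardiogram (Safety outcomes), which contact alone does not supply. Removal is likely but not established.
- **The rule cannot be applied to controls.** Controls have a 14-day standard therapy, all medication is recorded, and the visit, violation and data conditions apply to both arms. Compliance is undefined there, not impossible.
- **The PPS would hide harm.** An example can be built, with invented counts for 80 per arm: 16 against 8 deaths and 44 against 49 improved give 55.0% − 61.3% = −6.3 points in all patients, but 44/64 − 49/72 = +0.7 after dropping deaths. Remove 20 improved early discharges per arm too and it is 24/44 − 29/52 = −1.2; with 30 it is 14/34 − 19/42 = −4.1. Mortality is also a separate secondary outcome, and the FAS would still show −6.3.

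**Conclusion.** The point holds for the PPS definition alone. Exclusion of patients who die before day 14 follows directly from the text. Exclusion of early discharges is possible. The compliance range is undefined in the control arm, so that screen may select in one arm only. The PPS is therefore conditioned on post-randomisation outcomes and is at risk of bias.

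A reader might infer that the PPS is biased in favour of the granule. The documents do not support that: dropping deaths raises an arm's rate, dropping discharges lowers it, and equal removal with no effect leaves no difference. The 3.6-point and 8.5-point differences, and the range of +3.2 to +15.3 points, rest on assumed shares and show scale only. The intention-to-treat FAS is not affected, so this is a correction worth making to a supporting analysis and not a threat to the main one.

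**What to change.** Amend the PPS definition before the analysis:

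- Count death or discharge before day 14 as completed follow-up, with the outcome retained (death as level 6, discharge as level 1).
- In the granule arm, compute adherence as sachets taken divided by sachets due until death, discharge or day 14, whichever comes first.
- In the control arm, replace the percentage with the criterion that the patient did not receive Shenhuang granule.
- State that the conclusion rests on the FAS, meaning all randomised patients analysed as randomised, and that the PPS is a sensitivity analysis.

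The cost is statistical text only. No patients, visits or measurements are added, and treatment does not change.

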**Methods/design:**

This multicenter, open-label randomized controlled trial is conducted in 160 participants with severe COVID-19. The participants will be randomly (1:1) divided into treatment group or control group. All participants are given standard therapy at the same time. The experiment will receive Shenhuang granule treatment twice a day for 14 days. The clinical indicators of patients will be assessed at baseline and at 3, 5, 7, and 14 days after treatment initiation. The primary outcome is 14-day clinical outcome. Adverse events will be monitored throughout the trial.

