### Outcomes and measurements

The primary outcome is clinical improvement up to 14 days after treatment. The definition of clinical improvement is that the patient’s admission status drops by 1 point on the 6-point scale or is discharged from the hospital, whichever comes first. The 6-point ordinal scale based on the well-defined WHO severity scale is as follows: 6 = death; 5 = critical, meet any of the following conditions: (1) respiratory failure, mechanical ventilation is required, (2) shock, (3) with other organ failure which requires ICU care; 4 = severe, meet any of the following criteria: (1) respiratory distress (≥ 30 breaths/ min), (2) oxygen saturation at rest ≤ 93%, and (3) arterial partial pressure of oxygen (PaO_2_)/fraction of inspired oxygen (FiO_2_) ≦ 300 mmHg; 3 = moderate, fever and respiratory symptoms, accompanied by radiological findings of pneumonia; 2 = mild, mild clinical symptoms, and no imaging signs of pneumonia; and 1 = discharged alive, (1) body temperature returned to normal for more than 3 days, (2) respiratory symptoms improved markedly, (3) pulmonary imaging showed obvious absorption of inflammation, and (4) the nucleic acid test of respiratory tract specimen is negative for 2 consecutive times.

Secondary outcomes are the mortality and rate of receiving invasive ventilator in the severe category, the improvement of oxygen saturation, and Acute Physiology and Chronic Health Evaluation (APACHE-II) score.

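### Oxygen saturation and APACHE-II are called continuous but given a test and effect measures for categorical data, with no cut-point stated, so the analysis of two of the four secondary outcomes does not fit the data

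*Protocol article*

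**What the plan says.** The Outcomes and measurements section defines the primary outcome as a yes/no event: "The definition of clinical improvement is that the patient’s admission status drops by 1 point on the 6-point scale or is discharged from the hospital". It then lists four secondary outcomes: "Secondary outcomes are the mortality and rate of receiving invasive ventilator in the severe category, the improvement of oxygen saturation, and Acute Physiology", where the last item is the APACHE-II score. No threshold turns oxygen saturation or APACHE-II into a responder outcome, there or in the Discussion, which repeats the list.

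The Statistical analysis section makes four statements on method:

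- Variables labelled continuous: "For the continuous variables, the chi-squared test or Fisher’s exact test is used to compare the clinical improvement, oxygen saturation, and Acute Physiology" (the last item is again APACHE-II).
- Effect measures: "Relative risk, risk difference, and number of treatments are reported with a 95% confidence interval".
- Categorical variables: "For the two categorical variables, we make comparison between groups and calculate the 95% CI using chi-squared tests".
- Repeated measures: "For the repeated measures data, category variance outcomes are analyzed using generalized estimating equations".

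**The concern.** Chi-squared and Fisher's exact tests compare counts in categories. Applied to a score, they need either a cut-point, which the plan does not give, or a table with one column per distinct value, which ignores the order and spacing of the values. Relative risk, risk difference and number needed to treat have no meaning for a score until it has been dichotomised.

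Three things are at stake: power to detect a real difference in oxygenation or severity, an effect size that a clinician can read, and protection against a cut-point picked because it gives a favourable result.

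**Working it through.** **Step 1: outcomes against stated methods.**

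| Outcome | Type by its definition | Stated method | Fits? |
|---|---|---|---|
| Clinical improvement (primary) | Binary | Chi-squared/Fisher, under the continuous label | Method yes, label no |
| Mortality | Binary | Chi-squared (categorical sentence) | Yes |
| Invasive ventilation | Binary | Chi-squared (categorical sentence) | Yes |
| Oxygen saturation | Continuous, no threshold | Chi-squared/Fisher with RR, RD, NNT | No |
| APACHE-II | Integer score, no threshold | Chi-squared/Fisher with RR, RD, NNT | No |

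Placing mortality and ventilation under the categorical sentence is an inference, since that sentence names no outcomes. No t-test, rank test, ANCOVA or mixed model appears in the article. Generalized estimating equations can handle continuous data, but the sentence naming them restricts them to categorical outcomes.

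**Step 2: the plan's own figure.** The only sample size is for the binary primary outcome, "presuming that the rate of the clinical effective rate in the treatment group is improved from 61.11 to 91.18"%, with two-sided alpha 0.05 and power 90%. The pooled formula is

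n = [1.960·√(2·p̄·(1−p̄)) + 1.282·√(p₁(1−p₁)+p₂(1−p₂))]² / (p₂−p₁)²

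With p₁ = 0.6111, p₂ = 0.9118 and p̄ = 0.76145, n = (1.181 + 0.723)² / 0.3007² = 40.1. This rounds up to 41 per group, as stated, so the present point does not touch the sample size. The article gives no power, SD or effect size for oxygen saturation or APACHE-II. Everything below rests on assumptions.

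**Step 3: information kept by a cut-point.** For a normal variable cut at quantile q, with c the normal deviate of q, the efficiency relative to a comparison of means is φ(c)² / [q(1−q)].

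- Median: 0.3989² / 0.25 = 0.637, a loss of about 36%.
- 75th percentile: 0.539, a loss of about 46%.
- 80th percentile: 0.490.
- 90th percentile: 0.342.

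More than half is lost only when the cut leaves about 20% or fewer on one side.

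**Step 4: power at 80 per arm (160 randomised 1:1), assumed difference 0.5 SD, two-sided 0.05.**

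- Comparison of means: Φ(0.5·√(80/2) − 1.960) = Φ(1.202) = 0.885.
- Median split: proportions 0.500 and Φ(0.5) = 0.691. The null SE is 0.0776 and the alternative SE is 0.0761, so Φ[(0.1915 − 1.960·0.0776)/0.0761] = Φ(0.518) = 0.698.
- Cut at the 75th percentile 0.678; at the 90th 0.528.
- With 10% dropout (80 × 0.9 = 72 per arm): 0.851 for means, 0.651 for a median split.
- Patients per arm for 80% power: 63 for means, 102 for a median split, 152 for a cut at the 90th percentile.

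**Step 5: chi-squared on every distinct value.** Simulation at 80 per arm and a 0.5 SD difference, with normal scores rounded to integers, gives power of 0.315 at SD 3, about 0.15 to 0.16 at SD 6, and 0.126 at SD 7. A t-test on the same kind of data gives 0.88. For a saturation-like measure (SD 2.5, capped at 100) raw-value power is 0.37 to 0.43, depending on the assumed mean.

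**Step 6: type I error.** With no true effect, a split at the pooled median rejects 4.7% to 5.1% of the time, and raw-value chi-squared 2.4% to 2.6%. Searching every integer cut between the 10th and 90th percentiles and keeping the best gives about 30% to 31% false positives for an APACHE-II-like score and 20% to 21% for a saturation-like measure.

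**The case against.** The strongest reply is that this is a drafting slip. The sentence also calls clinical improvement continuous, although it is binary and the named test suits it, so a continuous-data sentence and a categorical one may have been merged. That is plausible and explains the mismatch. It does not remove it, because the method for continuous data is still absent. Nor is this detail left to an unseen analysis plan: the article names a method, and the method does not fit.

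Four stronger readings are tempting, and the document does not support them.

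- **The analysis is invalid.** A chi-squared test on a responder definition fixed in advance keeps its type I error (Step 6), and improvement of oxygen saturation could be meant as a yes/no outcome. The fault is that no definition is given.
- **Most of the information is discarded.** That follows only from an extreme cut or from raw-value categories, which few statisticians would use on APACHE-II. A median split keeps about 64%.
- **The false-positive rate will be about 30%.** That needs a full search over cut-points using results by arm. No such search is planned, and the randomization section keeps evaluators and the statistician blinded until the analysis is complete. A cut taken from pooled, blinded data, such as the pooled median in Step 6, does not inflate the error.
- **A repeated-measures model is missing for two scores taken at every visit.** The abstract says only that clinical indicators are "assessed at baseline and at 3, 5, 7, and 14 days after treatment initiation". The schedule table is not shown, so the visits for these two measures are not known. The choice of covariates and model is also commonly left to an analysis plan.

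**Conclusion.** The point holds in a limited form. The Statistical analysis section labels three outcomes continuous and gives all three a categorical test with binary effect measures. For clinical improvement only the label is wrong. For oxygen saturation and APACHE-II the test and the effect measures do not fit the data, and the article offers no cut-point or alternative that would make them usable.

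The practical size depends on how the gap is filled. A central cut costs roughly a third to a half of the information, raw-value categories cost far more, and a cut chosen from results by arm would inflate false positives. The power figures assume normal data, 80 per arm and a 0.5 SD difference, none of which the document specifies for these outcomes. Only secondary outcomes are involved, and the primary test and sample size stand. It should be fixed, but it does not threaten the trial's main conclusion.

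**What to change.** Rewrite the method sentences in the Statistical analysis section along these lines:

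- Clinical improvement, mortality and invasive ventilation are binary outcomes, compared by chi-squared or Fisher's exact test, with relative risk, risk difference and number needed to treat, each with a 95% CI.
- Oxygen saturation and APACHE-II are continuous outcomes, compared by a baseline-adjusted difference in means with 95% CI, from ANCOVA or from a mixed model if they are measured at several visits. A rank test is used if the distribution is markedly skewed.
- Any responder definition for either measure is stated with its threshold and fixed before unblinding.

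The cost is a wording change made before unblinding. It needs no new data, no extra patients and no change to patient care.

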### Randomization, allocation concealment, and blinding

The randomization sequence is generated by SPSS 19.0, using permuted small blocks of random size, stratified by medical center, and grouping the Chinese medicine group and the control group on a 1:1 schedule. The two sets of allocation codes are kept in opaque envelopes; one set is kept by the research sponsor and the other set by the pharmacy administrators, who then assign the study drug to the nurses for administration. This is an open-label study. The allocation concealment is blinded before the envelop is opened. After randomization, subjects randomized to the intervention arm will be receiving combined Shenhuang granule and Western medicine therapy, or only Western medicine therapy. The evaluators and statistician will be blinded until the completion of the visit and analysis. The statistical analysis is carried out by the professors of statistics at the Shanghai University of Traditional Chinese Medicine.

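### The primary test of 14-day improvement uses no baseline covariates; it is valid, but it gives up some precision that could be had at almost no cost

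*Protocol article*

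**What the plan says.** The Protocol article, Statistical analysis, fixes the primary comparison: "the chi-squared test or Fisher’s exact test is used to compare the clinical improvement". That sentence is introduced as covering continuous variables, but a later sentence on categorical variables also gives chi-squared, so both lead to the same kind of test. For effect sizes it says: "Relative risk, risk difference, and number of treatments are reported with a 95% confidence interval". No baseline covariate is named for the test or the estimates. Generalized estimating equations are kept for repeated measures.

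The same article shows what baseline information exists:

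- Abstract, Methods/design: "The clinical indicators of patients will be assessed at baseline".
- Inclusion criteria: adults up to age 80 who meet any one of three severity criteria, with no upper limit on severity.
- Outcomes and measurements: improvement is counted from the status at admission. Improvement in oxygen saturation is a secondary outcome, which needs a baseline value.
- Randomization, allocation concealment, and blinding: the sequence is generated "using permuted small blocks of random size, stratified by medical center". Severity and age are not stratified.

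**The concern.** Patients can enter anywhere from just past a severity cut-off to much sicker, and across a wide age range. Both plausibly predict who improves by day 14. The endpoint is also defined relative to the starting level: the entry criteria match level 4 of the scale, but nothing excludes a patient already at level 5, who would cross a different threshold to count as improved.

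Stratifying by centre leaves severity and age to chance. A test that ignores them leaves outcome variation unexplained that the trial has the data to explain. At stake are the width of the promised confidence intervals, the power if the effect is smaller than planned, and the temptation in an open-label trial to adjust after the fact if one arm looks sicker.

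**Working it through.** **Reproducing the plan's figure.** The Sample size section takes rates of 61.11% and 91.18% ("presuming that the rate of the clinical effective rate in the treatment group is improved from 61.11 to 91.18"), two-sided alpha 0.05 and beta 0.1, and reports that "we calculated that 41 patients should be recruited in each group". With pooled variance under the null and no continuity correction:

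n = [1.960·√(2·p̄·q̄) + 1.282·√(p₁q₁ + p₂q₂)]² / (p₂ − p₁)²

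- p̄ = (0.6111 + 0.9118)/2 = 0.7615, so √(2·0.7615·0.2385) = 0.603
- √(0.2377 + 0.0804) = 0.564
- n = (1.181 + 0.723)² / 0.3007² = 40.1, rounded up to 41. This agrees.

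**Power of the planned test at the enrolled size.** The same formula solved for power gives Φ[(0.3007·√n − 1.181)/0.564]:

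- 80 per arm: Φ(2.67) = 99.6%
- 72 per arm (80 less the stated 10% drop-out): Φ(2.43) = 99.2%

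**What adjustment adds to power.** The document does not say how strongly severity or age predicts improvement, so this is an assumed range. Trials were simulated with one standard-normal prognostic score, a logistic outcome model, and marginal rates held fixed.

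At the planning rates (8,000 trials per cell, adjusted likelihood-ratio test against chi-squared):

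| AUC of score (assumed) | Gain, 80 per arm | Gain, 72 per arm |
|---|---|---|
| 0.63 | 0.0 points | 0.2 points |
| 0.70 | 0.2 | 0.2 |
| 0.74 | 0.1 | 0.3 |
| 0.79 | 0.3 | 0.4 |

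At a smaller, assumed effect of about 61% vs 79% (80 per arm, 4,000 trials per cell, standardised risk difference against chi-squared):

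| Log-odds per SD (assumed) | Unadjusted power | Adjusted power | Gain |
|---|---|---|---|
| 0.7 | 71.6% | 75.4% | 3.8 points |
| 1.0 | 72.0% | 79.1% | 7.1 |
| 1.3 | 72.4% | 82.6% | 10.2 |

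A weak score (log-odds 0.4) gains about 1 point. Repeat simulations put the top of the range near 11 points.

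**What adjustment adds to precision.** This gain does not depend on power. At the planning rates, the unadjusted risk difference has about 2% (log-odds 0.4) to 22% (log-odds 1.3) more variance than the standardised one. Its standard error at 80 per arm is √[(0.2377 + 0.0804)/80] = 0.063, so the 95% CI is about ±12.4 points. Dividing by √1.02 and √1.22 gives about ±12.2 and ±11.2 points.

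**Validity under no difference.** Chi-squared rejected in 4.5% to 5.5% of simulated trials and Fisher's test in 2.9% to 3.6%. The test on the standardised risk difference rejected in 5.4% to 5.9%, and the adjusted likelihood-ratio test in 4.7% to 5.8%.

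**Chance imbalance.** For a standardised covariate, the difference in arm means has SD √(2/80) = 0.158, so the probability of an imbalance above 0.3 SD is about 6%.

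**The case against.** The strongest reply is that an unadjusted chi-squared test is a standard, unbiased choice for a binary outcome in a randomised trial, that it contradicts nothing in the protocol, and that at the protocol's own effect there is almost no power left to gain. All of that stands. Covariate lists are also often left to an analysis plan. That part carries less weight, because the article does name the primary test.

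A reader might infer two stronger things, and the document supports neither:

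- *That the trial gives up several points of power.* This needs a true effect well below the planned 30 points and a moderate to strong predictor. Neither is in the document.
- *That chance severity imbalance biases the result.* Over repeated randomisation it is variance, which the test and the confidence intervals already reflect. Adjustment helps in the particular trial where an imbalance occurs; it does not repair an invalid analysis.

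Three further limits stand. A P/F ratio is not shown to exist for every patient, since any one of three criteria qualifies and the assessment table is not shown. Part of any apparent gain over Fisher's test (about 5 to 7 points at effects of 10 to 20 points) comes from that test's conservatism, not from ignoring covariates. And the simulations used one prognostic score, not the full model. At the planning rates only about 80·0.3889 + 80·0.0882 ≈ 38 patients would not improve, so the model must stay small.

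**Conclusion.** The point holds as an efficiency improvement, not as an error. The named primary analysis is valid but uses none of the baseline information available. At the protocol's own rates the cost is about 2% to 22% more variance in the risk difference and under 1 point of power. At an assumed 61% vs 79% it is about 1 to 11 points of power. Both ranges rest on assumed covariate strengths (log-odds 0.4 to 1.3 per SD); with a weak predictor the benefit is negligible. Because the planned 30-point effect is taken from a single cited study, it is reasonable to look at smaller effects, but only as a stated assumption.

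**What to change.** Before any outcome data are examined by arm, specify as the primary analysis a logistic model of 14-day clinical improvement on arm, baseline oxygen saturation, age and centre. Add baseline scale level if enrolled patients differ on it. Use the P/F ratio only if it is recorded for all patients. Report the covariate-standardised risk difference and relative risk with 95% CI, and keep the chi-squared test as a supportive analysis.

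State which test of the arm effect gives the primary P value. With about 38 non-improvers expected at the planning rates, also state what is dropped or pooled if the model does not fit, for example scale level first and then small centres.

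The cost is analysis-plan wording and slightly more analysis work; design, sample size and patient care do not change. The trade-off is a type I error that may run slightly above nominal at this size, about 5% to 6% in simulation.
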